### 2.6. Data Collection

Since the participants will be recruited from the breast and prostate cancer clinics and the rheumatology clinic, the medical history that appears in the EPIC electronic medical record will be available for review prior to enrollment per IRB approval (OHSU IRB#00023183) and cross-checked with the participants after we have obtained informed consent on the day of the SFIT intervention. This will serve as the start of the data collection process for determining inclusion/exclusion of participants (see Section 2.2.1, Table 1; Inclusion and Exclusion for SFIT for Breast and Prostate Patients and Inclusion and Exclusion for SFIT for Axial Spondyloarthritis Patients) and baseline data collection (see Section 2.6.1, Section 2.7, and its subsections, and Section 2.8 and its subsections). Case report forms will be used to capture participant baseline and data collected at all pertinent time points per protocol and will serve as a hard-copy record of data, which we will enter into a research electronic data capture system, as required by our university.

#### 2.6.1. Baseline

Demographic data collection will occur prior to the start of both SFIT intervention studies and will be specific to each population of interest [93]. The behavioral/psychological measures, biological measures, and feasibility measures will be collected prior to placement of the participant in the SFIT intervention room.

#### 2.6.2. Follow Up

Follow-up data collection will be within the 3–4-day period after the SFIT intervention and in study #1 participants with breast or prostate cancer and will include blood specimens for CBC with differential counts of leukocytes, NK cell phenotyping and plasma for perforin and granulysin ELISAs [6]. We will survey the participants on events that might affect immune response. Every effort will be made to minimize the amount of blood drawn. Data collection will occur immediately after the intervention for study #2 participants with AxSpA and include the same measures as baseline as well as the intervention fidelity measures. Follow up will also include collection of adverse events, serious adverse events, and unanticipated problems, per IRB protocol for intervention studies.

### 2.7. Measures—Behavioral/Psychological

To measure the impact of SFIT on patients with chronic or breakthrough pain due to axial spondyloarthritis (axSpA), scales which interpret the direct effect on symptoms of pain, psychological distress, and physical functionality specific to axSpA will be used. These include the Visual Analog Scale for pain [94,95], the Depression, Anxiety, and Stress Scale [96,97], and the Bath Ankylosing Spondylitis Disease Activity Scale [98].

#### 2.7.1. Demographics

Demographic characteristics of participants will include clinically relevant ethnographic details specific to assigned sex (male or female), race, and ethnicity. Diagnostic information specific to axSpA, including date of diagnosis and onset of symptoms (date), chronicity of symptoms (in months), and non-biologic medication management (name of medication/last date of use), will be ascertained. Since culture, religion, and personal belief systems influence perception of pain, depression, stress, and functionality, we will include questions about these three pertinent individual characteristics in our baseline demographic data collection [99].

#### 2.7.2. Visual Analog Scale (VAS)

The VAS is a widely used self-reported tool measuring present-state perceived pain intensity [100]. Patients will be asked to indicate their perceived pain intensity along a 10 cm horizontal line (which can be on paper or computerized), and this rating will then be measured from the left edge up to the indicated marking to represent the level of pain intensity. The line represents a continuum between “no pain” and “worst pain”. The VAS is often used in clinical settings and is sensitive in determining the effect of comfort or pharmacological interventions [94]. The VAS has performed well on psychometric tests of validity (for example, η^2^ = 0.47; F = 0.44 [94,101]), and reliability (r_s,VAS_ = 0.52–0.89 [102]) for measuring pain clinically. VAS scores will be treated as ratio data [103].

#### 2.7.3. Depression, Anxiety, and Stress Scale (DASS)

The DASS comprises a set of three self-report scales, which are intended to measure clinically significant symptoms of emotional states of depression, anxiety, and stress [96,104]. Each of the three DASS scales (depression, anxiety, and stress) contains 14 items, divided into subscales of 2–5 items measuring the same construct, for a total of 42 items. The participants will be asked to complete the DASS prior to and immediately after the SFIT intervention. The DASS, which is intended to measure symptom severity of self-reported negative emotional states, including depression, anxiety, and stress, shows good psychometric validity and reliability (Cronbach’s *α* = 0.89; test–retest and split-half reliability scores are r_DASS_ = 0.99 and 0.96, respectively [96]) as a dimensional measurement of psychological distress associated with chronic conditions [104].

#### 2.7.4. Bath Ankylosing Spondylitis Disease Activity Index (BASDAI)

The BASDAI is commonly used to measure clinical symptoms of AS and axSpA, including fatigue, spinal pain, joint pain related to swelling, and enthesitis, or inflammation of the tendons and ligaments, as well as morning stiffness duration and severity [105]. It consists of 6 self-report questions, with each question scored from 1, representing “none” or no symptoms, to 10, representing “the worst”, with the score from the questions pertaining to morning stiffness and duration averaged such that 5 questions in total are scored. The participants will be asked to complete the BASDAI prior to and immediately after the SFIT intervention. The resulting score (from 0 to 50) is divided by 5 to give a final BASDAI score of 0–10, with scores of 4 or greater indicating significant disease [106]. The BASDAI has demonstrated extraordinary reliability at *p* < 0.001 [105]. In a test of validity of the BASDAI for AS patients, Cronbach’s *α* = 0.786 [98].

### 2.8. Measures—Biological/Immune System

We will use established pre-clinical and clinical measures to characterize the immune responses before and after the simulated forest exposure intervention.

#### 2.8.1. Demographics

Demographic characteristics of participants will include clinically relevant ethnographic details specific to age, assigned sex (male or female), race, and ethnicity, and history of smoking.

#### 2.8.2. CBC and Differential Cell Count

Complete blood count (CBC) and differential cell counts will be measured at baseline (prior to implementation of the simulated forest exposure intervention) and at Day 3. Correlation between this clinical measure and the data from flow cytometry and ELISA (outlined below) will be conducted to translate the pre-clinical findings into clinical use. A whole blood sample for a CBC with a differential cell count will be collected two times using a 4 mL EDTA tube, prior to the SFIT intervention and on Day 3 after the SFIT intervention. This measure will include WBC count and percentages of 100 cell counts and absolute counts for neutrophils, lymphocytes, and monocytes. The clinical core laboratory at OHSU complies with established inter- and intra-assay parameters as it is accredited by Clinical Laboratory Improvement Amendments.

#### 2.8.3. Flow Cytometry for NK Cell Number and Activity

Flow cytometry is used to monitor immune system changes tied to specific disease states, which makes it ideal for defining cellular responses of interest [107]. NK CD3^−^/CD56^+^ and NK CD3^−^/CD56^+^/CD69^+^, (i.e., NK number and activity, respectively) will be measured by flow cytometry immunophenotyping using freshly collected peripheral whole blood (approximately 4 mL). Cells will be prepared for flow cytometry using the standard fluorescence-activated cell sorting method. Data analysis will be performed by gating on live cells based on forward versus side scatter profiles, then on singlets using forward scatter area versus height, followed by cell-subset-specific gating [107].

#### 2.8.4. Perforin Expression

Perforin expression will be measured by an enzyme-linked immunosorbent assay (ELISA) and will be used to monitor downstream perforin secretion due to NK cell activity [27]. Perforin will be measured using plasma extracted from whole blood, which will be frozen at −80 °C and stored until needed for the assay. Optimized ELISA kits from ThermoFisher Scientific, Waltham, MA, USA, will be used per manufacturer instructions to detect perforin levels. The enzyme-dependent color change will be read out on a Multi-Mode Mircroplate Reader. Perforin concentration will be extrapolated from the standard curve [108].

#### 2.8.5. Granulysin Expression

Granulysin expression will be measured by an enzyme-linked immunosorbent assay (ELISA), which will be used to monitor downstream granulysin secretion due to NK cell activity [27]. Granulysin will be measured using plasma extracted from whole blood, which will be frozen at −80 °C and stored until needed for the assay. Optimized ELISA kits from AbCam, Cambridge, MA, USA, will be used per manufacturer instructions to detect granulysin levels. The enzyme-dependent color change will be read out on a Multi-Mode Mircroplate Reader. Granulysin concentration will be extrapolated from the standard curve. For both perforin and granulysin expression, we will need 4 mL of freshly collected peripheral whole blood [108].

### 2.9. Follow-Up Measures Day 3

In addition to collecting whole-blood specimens for CBC with differential, NK cell number and activity, perforin, and granulysin, we will note any unanticipated problems, adverse events and serious adverse events affecting the participants per IRB protocol for intervention studies. Unanticipated problems will be determined with the assistance of the clinicians and the study team as these are determined through a ranking procedure specified by our university’s Office of Human Research Protections. Adverse events will include subjective or objective symptoms occurring spontaneously, significant clinical lab abnormalities, a worsening of the participants condition from baseline, are recurrence or increase in signs and symptoms of original disease that occur after the SFIT intervention and are worsened or changed in quality. Serious adverse events will include death, life-threatening adverse event, new hospitalization or prolongation of current hospitalization, or a new significant incapacity or new substantial inability to complete activities of daily living.

## 3. Discussion

We have presented our lab set up for the SFIT intervention. The SFIT intervention as described may be used in a multi-arm design with a control group, using VR only, phytoncide atomization only, or both in combination. We expect to use whatever combination is proven to be most effective as a minimally invasive intervention for all of the following designs in a stepwise progression: longer intervention duration to optimize dose effect; intermittent, but repeated intervention to optimize dose effect drop off; and home use application to move the optimized intervention into practical use.

An intervention using VR and humidified phytoncides, α- and β-pinene, and limonene, in a simulated forest exposure intervention as a substitute for forest bathing in AXSpA patients with chronic or breakthrough pain and cancer patients with early-stage solid tumors (HR + HER2- breast cancer and prostate cancer) who have completed surgery or chemo- and/or radiation therapy (exclusive of hormone therapy) is possible in a lab setting. Moving SFIT to a home setting may be challenging, but not insurmountable.

### 3.1. Expected Outcomes

The expected outcome for the future two studies is the creation of a standardized protocol for deploying SFIT. This will include calibration and measurement set points, cutoff criteria and describing how to maintain a consistent dose of phytoncide and ease the use of VR for participants. We expect to uncover pertinent adverse events, severe adverse events, and unanticipated problems. For study #1, we expect that the combined use of our three phytoncides of interest and VR will improve NK cell numbers and activity and blood levels of perforin and granulysin in patients with breast or prostate cancer. For study #2, we expect that the use of d-limonene and VR will reduce pain, stress, and depression in patients with axial spondyloarthritis.

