### 1.3. Purpose

If forest immersion can provide immune system benefits in healthy men (i.e., improved NK cell numbers and activity, increased perforin and granulysin), can dispersal of three phytoncides (α- and β-pinene and limonene in combination) paired with a greenspace virtual reality provide the same positive effects on NK cells in patients with solid tumor cancer who have completed cancer therapy? Additionally, can humidified limonene paired with virtual reality reduce pain and psychological stress in patients with axial spondyloarthritis? Our purpose is to deploy a standardized study protocol for simulated forest immersion intervention in cancer patients with NK cell depletion and patients with axial spondyloarthritis with chronic and breakthrough pain to test its feasibility and rigor. The simulated forest immersion intervention will provide greenspace/forest experience through three of the five senses. Virtual reality will provide visual and auditory stimuli. Humidified aromatic forest oils will provide olfactory stimuli. Virtual reality and atomized forest oils may be used in combination or alone [71]. Two distinct studies will use this standardized protocol for (1) cancer patients and (2) patients with axial spondyloarthritis. The purpose of this paper is to outline the development of the study protocol for the intervention and the control conditions of the clinical lab setting.

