### 2.3. Setting

The SFIT Lab is located in our Integrated Bio-Behavioral Lab space within our school. The lab room, where the instrumentation for the SFIT is set up, is 20 feet × 15 feet with a 12-foot ceiling. The room has temperature control, so a consistent temperature between deployments of SFIT with participants can be maintained, as well as lighting control, so the lights can be dimmed when patients are using VR.

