### 2.4. Intervention—Procedure

Our two studies are novel as no one to date has used simulated forest immersion in patients with acute or chronic morbid conditions. The principal investigator (PI) and research associate (RA) will implement SFIT in a separate room from the room used to cross-check inclusion and exclusion, obtain informed consent, collect baseline measures, and allow the participant to rest. Prior to the arrival of the participant, the SFIT intervention space will be prepared. Preparation of the intervention space includes calibration of the instruments that will measure volatile organic compound particles (phytoncides are volatile organic compounds) and droplets, room temperature and humidity, and room surface temperatures, followed by measurement of the ambient particles and droplets and room temperature and humidity prior to the implementation of the atomized phytoncides [71,81]. Phytoncides α-pinene, β-pinene, and d-limonene (Floraplex Terpenes, Ypsilanti, MI, USA) will be prepared for atomization with a commercially available atomizer (Asakuki 500 mL Premium Atomizer, Tronhon Co., Ltd., Chongqing, China) that can emit phytoncides for up to 3 h. Once the dose expected (0.80 ppm) reaches the dose published by Li [6], the participant will be brought into the intervention room. To date, the Li study, which was conducted with healthy men, has been the only study to record phytoncide dose in a controlled setting. We will use this concentration as the target dose for our humidified phytoncide set up. Both at the beginning and at the end of 1 h of exposure to the simulated forest immersion therapy intervention, ambient phytoncide in the contained space will be measured indirectly by measuring both the increase in ambient air particle mass and number, as well as by measuring the change in total volatile organic compounds (VOCs). Total particle numbers will be measured with a continuous ultrafine particle counter (P-Trak 8525, TSI, Shoreview, MN, USA), and the total VOCs will be measured with the portable handheld monitor (Mini ppbRAE 3000, Honeywell International INC.; San Jose, CA, USA). The P-Trak and Mini ppbRAE 3000 will measure the increase in particle numbers and water droplets (aerosol), respectively, which will serve as a surrogate of relative exposure to phytoncide. Continuous monitoring of room temperature and relative humidity will be measured by the HOBO MX2301 Temperature/RH Data Logger (ONSET, Bourne, MA, USA). Room surface temperature will be measured by ADC Adtemp Mini 432 Non-Contact Infrared Thermometer (American Diagnostic Corporation, Hauppauge, NY, USA). VR will be provided by VIVE Pro Eye, HTC (high-tech computer) Corporation, (New Taipei City, Taiwan) with digital rendering of forested greenspace. Once 1 h of SFIT concludes, the participant will be removed to the preparation area and given instructions related to reporting unanticipated problems, adverse events, and serious adverse events, and an appointment to return for follow up on Day 3. See Figure 1, which illustrates the SFIT process/procedure.

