##### Asakuki 500 mL Premium Atomizer, Tronhon Co., Ltd., Chongqing, China

The atomizer holds 500 mL of liquid that can be atomized over 3 h. Of that 500 mL, a portion will be reduced that coincides with the amount of phytoncide that will be added. We expect that we will add 30 mL per phytoncide to the atomizer to achieve the detectable published amount [6,21]. Mist will be created by an ultrasonic plate within the atomizer, and the mist will be adjusted for a weak mist or a strong mist. Choice of weak or strong mist will be adjusted to fit the published detectable amount of phytoncide. Mist time can be regulated to maintain 60, 120, and 180 min of operation. We will use a 60 min mist time with the participants of study #1 and study #2. A fan within the atomizer will disperse the mist into the room. Room temperature and humidity will be monitored continuously as low temperature and high humidity may condense the mist into water droplets [87], which is to be avoided to allow for accurate dose calculations.

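### Study #2's phytoncide composition is inconsistently specified, and the single 0.80 ppm target does not say what it refers to in each study

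*Protocol article*

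**What the plan says.** All references are to the protocol article.

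**Statements that assign an agent to a study.** Section 1.3 (Purpose) asks "can humidified limonene paired with virtual reality reduce pain and psychological stress in patients with axial spondyloarthritis". Section 3.1 (Expected Outcomes) gives the mixture to the cancer study, "For study #1, we expect that the combined use of our three phytoncides of interest and VR will improve NK cell numbers", and limonene to the other: "For study #2, we expect that the use of d-limonene and VR will reduce pain, stress, and depression".

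**Statements that do not separate the studies.** Section 2.4, the procedure for both, lists α-pinene and β-pinene "and d-limonene (Floraplex Terpenes, Ypsilanti, MI, USA) will be prepared for atomization with a commercially available atomizer". Section 3 (Discussion) describes an intervention with VR, α- and β-pinene "and limonene, in a simulated forest exposure intervention as a substitute for forest bathing in AXSpA patients" and in cancer patients.

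**Dose.** Section 2.4 brings the participant in "Once the dose expected (0.80 ppm) reaches the dose published" in a study of healthy men. That one figure serves both studies. The atomizer subsection of 2.4.1 says: "We expect that we will add 30 mL per phytoncide to the atomizer to achieve the detectable published amount". It also gives a capacity of 500 mL atomized over 3 h, a 60 min mist time for both studies, and a choice of weak or strong mist to fit the published level. Exposure is read from total particle counts and total VOCs.

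**The concern.** The name of the agent is part of study #2's hypothesis. If the three-compound mixture is delivered, a change in pain, stress or depression cannot be credited to d-limonene with VR, because both pinenes were also present. The documents allow either delivery, depending on which section the staff follow.

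The target has the same problem. A concentration taken from earlier work needs a referent: the sum of the compounds, or each one. Sections 1 and 1.2.3 describe the humidification work in healthy men as using the three compounds together. The article does not say what 0.80 ppm means when only limonene is in the air. The two studies may therefore share a number without sharing a dose definition, although section 1.3 presents the protocol as standardized across both.

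The measurements do not settle this. Section 2.4 calls them an indirect surrogate of relative exposure, and section 2.4.1 calibrates the VOC monitor with isobutylene. As described, neither instrument distinguishes limonene from the pinenes, so the logs could not show afterwards which composition a participant inhaled.

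**Working it through.** **1. Composition, section by section.**

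| Place | Agent for axial spondyloarthritis |
|---|---|
| 1.3 Purpose | limonene with VR |
| 3.1 Expected Outcomes | d-limonene with VR |
| 2.4 Procedure | all three prepared, no split by study |
| 3 Discussion | all three, both populations together |

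The first two rows agree with each other. They conflict with the Discussion, and the operative procedure does not carry the distinction they make.

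**2. Load, from the article's own figures.** Load = 30 mL × number of phytoncides; share = load / 500 mL.

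- Three: 30 × 3 = 90 mL; 90/500 = 18%.
- One: 30 × 1 = 30 mL; 30/500 = 6%.

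At equal mist output, total phytoncide emitted differs 3:1 while the target stays at 0.80 ppm.

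**3. What the target could mean** (assuming equal airborne shares when three are used).

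- Limonene alone at 0.80 ppm: limonene 0.80 ppm.
- Mixture, target as a total: limonene 0.80/3 = 0.27 ppm.
- Mixture, target per compound: limonene 0.80 ppm, total 3 × 0.80 = 2.40 ppm.

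Limonene exposure and total exposure can each differ threefold with the reading.

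**4. Illustrative mass balance of load against target.** The article does not derive 0.80 ppm from the load, so there is no calculation of its own to reproduce.

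*From the article:* the room is 20 feet × "15 feet with a 12-foot ceiling", so 20 × 15 × 12 = 3,600 ft³ = 101.9 m³; set temperature 70 °F; maximum output taken as 500/3 = 166.7 mL/h.

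*Assumed:* density 0.84–0.87 g/mL; molar mass 136.23 g/mol; 24.15 L/mol at 70 °F; emission in proportion to share of the liquid; even mixing; no surface loss.

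- Liquid equivalent of the target: 0.80 × 10⁻⁶ × 101,940 L / 24.15 × 136.23 = 0.46 g, or 0.53–0.55 mL.
- Emitted in one hour: 166.7 × 18% = 30 mL (three) or 166.7 × 6% = 10 mL (one).
- Full evaporation, no air exchange, density 0.84, three: 30 × 0.84 / 136.23 × 24.15 = 4.47 L of vapour; divided by 101,940 L this is 43.8 ppm. One: a third of that, 14.6 ppm.
- Full evaporation, 10 air changes/h, after one hour: about 43.8/10 = 4.4 ppm (three) or 14.6/10 = 1.5 ppm (one).
- Only 10% evaporating: from 4.4 ppm (three, no air exchange) down to 0.15 ppm (one, 10 changes/h).

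The full range, about 0.15 to 44 ppm, contains 0.80.

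**The case against.** The strongest reply is that every sentence assigning an agent to a named study agrees. Section 2.2 rests study #2 on animal d-limonene data, and the phytoncide subsection of 2.4.1 links d-limonene alone to pain and the mixture to NK cells. On this view section 2.4 is a shared materials list and the Discussion sentence is loose. Much of this stands: the intended reading is probably recoverable, and the section 3.1 sentence is not faulty taken alone. But section 2.4 is the only procedure given, and the Discussion sentence read literally says something else.

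A second reply is that a condensed article leaves preparation detail to a full protocol that is not shown. That would excuse silence. It does not excuse sections that disagree, in an article whose stated purpose is to outline the intervention protocol.

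A reader might also infer three stronger things, and the documents support none of them.

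- *That the exposure is undefined.* The study-specific sentences name an agent, and a numeric entry target and a 60 min duration are given.
- *That the 30 mL load cannot fit 0.80 ppm.* The load is an expectation, mist strength is adjusted to the published level, and dose is determined by air measurement. The calculated range spans the target and depends on evaporation, ventilation and mist output, which the article does not give.
- *That the level must rise during the hour rather than drop off.* This rests on the same assumptions. The planned before-and-after measurement would show a rise as well as a fall.

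It follows that exposure well above target is not an established safety finding.

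**Conclusion.** The point holds as an inconsistency in specification. Study #2's agent is limonene in sections 1.3 and 3.1, all three phytoncides in the Discussion, and not separated by study in section 2.4. One 0.80 ppm target covers both compositions without a stated referent, while the expected load differs threefold (90 mL or 18%, against 30 mL or 6%). The 3:1 ratio needs only the article's figures and equal mist output; the threefold spread in limonene level also needs equal airborne shares.

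The consequence is for attribution: as written, study #2 could deliver one agent and conclude about another, and the planned measurements could not tell them apart. The mass balance is secondary. It shows that overshoot is possible under some evaporation and ventilation assumptions, which justifies a check but is no proof of incompatibility.

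**What to change.** Reconcile sections 1.3, 2.4, 2.4.1 (atomizer), 3 and 3.1 so that:

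- each study has one stated phytoncide composition, repeated in the procedure;
- the meaning of 0.80 ppm, total or per compound, is stated for each study;
- the study #2 conclusion names the agent actually delivered.

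Which agent and dose apply is for the investigators; no view is taken here.

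Before the first participant, log an empty-room run of the full hour with each study's composition, to confirm that the expected load and continued misting hold the stated target.

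The cost is a few sentences of protocol wording and equipment runs with instruments already in hand.
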